**Methods/design:**

The study is a single-center, randomized controlled trial. A total of 240 participants will be randomly divided into four groups. The control group will receive standard antiemetic only, whereas three acupuncture groups will receive four electro-acupuncture treatments once a day with the standard antiemetic. Acupuncture group I and II will receive distal-proximal point association (“Neiguan (PC6) and Zhongwan (CV12)”, and “Zusanli (ST36) and CV12”, respectively); Acupuncture group III will receive local distribution point association (“Shangwan (CV13) and CV12”). The primary outcome measures are the frequency and distress of nausea and vomiting. The secondary outcome measures are the grade of constipation and diarrhea, electrogastrogram, quality of life, etc. Assessment is scheduled from the day before chemotherapy to the fifth day of chemotherapy. Follow-ups are performed from the sixth day to the twenty-first day of chemotherapy.

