#### Primary outcome measures

The primary outcome measures are as follows:Frequency of nausea and vomiting: total nausea and vomiting episodes per person over the 6-day study period will be recorded. The frequency of nausea and vomiting is the most valuable measurement for evaluation.Grading of nausea and vomiting: nausea and vomiting will be graded by Common Terminology Criteria for Adverse Events Version 4.0 [12].Rhodes Index of Nausea, Vomiting and Retching: nausea, vomiting and retching will be measured as separate entities by Rhodes Index of Nausea, Vomiting and Retching, which have 8 items with 5-point Likert scales. The frequency and distress of all entities are measured, as well as the duration of nausea and the amount of vomitius. [13]

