### Sample size calculation

A sample size calculation was performed based on the result of a trial by Shen J [8] and the results of a pilot study. To detect a significant difference between any two groups with a power of 90 % and type I error of 5 %, the calculated number of patients is 192. Considering a 20 % drop-out rate, the total sample size needs 240 patients and 60 patients in each group.

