### Statistical analysis

Statistical analysis will also be performed by the Clinical Evaluation Center at China Academy of Chinese Medical Science. The statistician is blinded from the allocation of groups. The Kruskal-Wallis test will be employed in the analysis of skewed distribution data. Chi-square analysis will be used for categorical variables, and Analysis of variance (ANOVA) for numerical variables. Repeated measures analysis will be used in the different time point assessment. A *P* value less than 0.05 is regarded as statistically significant.

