## Discussion

This study protocol expands current literature regarding the efficacy of acupuncture on CINV. Previous reviews showed that acupoint stimulation has a certain effect on CINV. However, the effects of different acupoint combinations are inconsistent. We designed our trial to compare the effects of distal-proximal point association and local distribution point association.

More than 300 acupuncture points are located on the body and each point has its own therapeutic indication. The correct selection and combination of acupoints are the keys to the curative effects of acupuncture [6]. Before developing the trial protocol, we screened a range of published articles and ancient books. Our literature search showed that PC6, ST36, and CV12 are the most commonly used acupoints for managing CINV [16, 17]. We selected PC6 and ST36 as the distal acupoints, and CV12 as the local acupoint. Based on the theory of Chinese acupuncture, distal-proximal acupoint association and local distribution point association are the two classic methods for combining acupoints. Distal-proximal acupoint association is also the most commonly used method in clinical applications. In this trial, there are three different acupuncture groups: “PC6 and CV12” and “ST36 and CV12” are the two disal-proximal acupoint association groups, and “CV12 and CV13” is the local distribution point association group. Therefore, we expect that distal-proximal point association (“PC6 and CV12” or “ST36 and CV12”) will have better effect than local distribution point association (“CV12 and CV13”). Furthermore, we can screen the most effective acupoint combination for clinical application from these three groups.

Although the manipulators and participants cannot be blinded to the group allocation in this study, all outcome measures will be administered and collected by a blinded estimator, and statisticians blinded to group assignment will perform data analysis. With respect to clinical quality control, the manipulators, estimators and statisticians will work independently to reduce the adverse impacts of artificial factors on data. A third party has been invited to manage data independently and to design a central randomization system for minimizing bias and enhancing clinical research quality.

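### Three primary outcomes in four arms are all judged at P < 0.05, so no family-wise 5% error is kept if a result on any primary measure can support a claim

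*Protocol article*

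**What the plan says.** - **Primary outcomes.** The Primary outcome measures section lists three: total episodes of nausea and vomiting over six days, CTCAE version 4.0 grade, and the eight-item Rhodes Index, which treats nausea, vomiting and retching separately. It adds that "The frequency of nausea and vomiting is the most valuable measurement for evaluation", but attaches no test order or error allocation to that remark.
- **Abstract.** The set is described differently there: "The primary outcome measures are the frequency and distress of nausea and vomiting". This covers the episode count and part of the Rhodes Index, and leaves out CTCAE grade.
- **Comparisons.** The Sample size calculation section is worded "To detect a significant difference between any two groups with a power of 90 % and type I error of 5" per cent. Four arms give six pairs. The Hypothesis section expects distal-proximal association (groups I and II) to do better, and the Discussion expects it to beat local association (group III). The Discussion also says that "we can screen the most effective acupoint combination for clinical application from these three groups".
- **Tests and threshold.** The Statistical analysis section names Kruskal-Wallis, chi-square, ANOVA and repeated measures analysis. It applies one rule throughout: a P "value less than 0.05 is regarded as statistically significant".

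**The concern.** The trial is meant to produce pairwise statements: which acupuncture arm beats control, whether groups I or II beat III, and which combination is best. Three primary measures and six pairs give 18 possible comparisons, all facing the same unadjusted threshold. An omnibus test cannot by itself support any of these statements, so some pairwise step has to follow it.

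At stake is a named combination put forward for clinical use because it crossed 0.05 on one of several measures, when the arms may not differ. Gating by an omnibus test gives little protection in the situation the trial expects. Once acupuncture beats control, the omnibus test is nearly always significant, and the three pairs among the acupuncture arms are then tested with no further safeguard.

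**Working it through.** **Inputs from the article.** Four arms at 1:1:1:1; three primary outcomes; threshold 0.05; 90% power; 5% type I error; "the calculated number of patients is 192"; 20% drop-out; total 240.

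**Reproducing the stated total.** 192 / (1 - 0.20) = 240, or 60 per arm, as stated. Evaluable per arm: 192 / 4 = 48. The 192 itself cannot be rebuilt, because the article gives no effect size or SD.

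**Implied effect.** For two means, two-sided 5%, 90% power and 48 per arm: d = (1.96 + 1.2816) × √(2/48) = 0.66 SD. This is a back-calculation used for illustration, not a figure in the article.

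**Assumptions.** Normal outcomes, equal variances, two-sided tests, and a common between-outcome correlation (not given in the article) ranging from 0 to 0.9. The rates come from simulation of 4 arms × 48 patients with pooled-variance F and t tests, 20,000 to 40,000 trials per setting. Separate runs differ by about half a percentage point.

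**Analytic anchor.** Three independent tests at 5%: 1 - 0.95³ = 14.3%. Treating all 18 pairwise tests as independent gives 1 - 0.95¹⁸ = 60%, which overstates the rate because pairs share arms; the simulation allows for this.

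**Chance of at least one false claim**

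| How the tests are run | Correlation 0 | 0.5 | 0.7 | 0.9 |
|---|---|---|---|---|
| Three omnibus tests, all arms equal | 14% | 13% | 11% | 8-9% |
| Pairs only after a significant omnibus test, all arms equal | 14% | 13% | 11% | 8-9% |
| All 18 pairs, unadjusted and ungated, all arms equal | 49% | 44% | 39% | 31% |
| Pairs among three identical acupuncture arms, omnibus-gated, control 0.66 SD worse, three outcomes | 32% | 28% | 25% | 19% |

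On a single outcome, six unadjusted pairs give about 20%. On a single outcome in the gated setting of the last row, the rate is about 12%; the omnibus test is significant in about 92% of those trials, so the gate is nearly always open.

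**Power cost of adjusting.** At d = 0.662 and 48 per arm, d × √(48/2) = 3.243.

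- Unadjusted: Φ(3.243 - 1.960) = 90%.
- Bonferroni over six pairs (0.05/6 = 0.0083, critical value 2.638): Φ(3.243 - 2.638) = 73%.
- Restoring 90% under that correction takes 71 evaluable per arm: 4 × 71 = 284 evaluable, and 284 / 0.8 = 355 before drop-out.

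**The case against.** - **The tests named are omnibus tests.** The Statistical analysis section specifies no pairwise test, so a reader might infer a false-claim rate of 30-50% from the plan, but the text does not establish it. That range needs 18 pairwise tests with neither adjustment nor gating. The tests actually named give about 8-14% when all arms are equal. This objection stands as to size. It does not remove the problem, since 8-14% is still above 5% and omnibus tests do not answer the pairwise questions the trial poses.
- **The 5% in the sample-size section is per comparison.** A reader might infer that the plan contradicts its own type I error. It does not: that 5% is attached to a two-group difference and is never described as family-wise.
- **The success rule is not written down.** The article does not say that one significant measure suffices, or that all three are needed. The figures above apply to the any-measure reading. If all three had to succeed, the inflation across outcomes would not arise.
- **A post hoc or multiplicity method may sit in an analysis plan not shown.** That is fair, and its absence from the article is not the point. What the article does fix is three co-listed primary outcomes, an abstract that describes them differently, and one flat threshold.
- **The article ranks frequency informally.** It does, but the ranking has no consequence for testing.

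**Conclusion.** The point holds in this form: with three primary outcomes, pairwise and best-combination aims, and a flat 0.05, a 5% family-wise error is not kept if any primary measure can carry a claim. The article does not fix the size. It runs from about 8-14% (omnibus tests only) to about 31-49% (all pairs, unadjusted and ungated). For the central question of differences among acupuncture arms, the omnibus-gated rate is about 12% on one outcome and 19-32% across three, if control is truly about 0.66 SD worse. All figures rest on 48 evaluable per arm, normal outcomes and the assumed correlation range. Testing the Rhodes entities or single days separately would raise them.

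**What to change.** 1. Make the six-day frequency count the single primary outcome, which follows the article's own ranking. Move CTCAE grade and the Rhodes Index to secondary, and bring the abstract into line.
2. Name one family-wise procedure at 5% covering all six pairs on that outcome. Holm works with rank tests if the counts are skewed; a Tukey-type method also gives simultaneous intervals. Choose one before unblinding.
3. Do not make the arm-versus-control tests conditional on I+II versus III. The first objective includes the efficacy of both associations. If all three acupuncture arms work equally, such a gate would open only 5% of the time. If only one of I and II beats III by 0.662 SD, the pooled contrast is 0.331 with standard error √(1/96 + 1/48) = 0.177, giving a gate power of about 46%.
4. Base any statement about the most effective combination only on the adjusted comparisons.
5. Restate the 90% power as per-comparison and unadjusted, or recalculate it.

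Cost: protocol and analysis-plan wording, with no new visits or data; the article reports recruitment as ongoing. Nominal P < 0.05 results on the demoted outcomes become supportive only. Power per pair falls to about 73% under Bonferroni at the implied effect, which Holm or a Tukey-type method would improve on somewhat, unless the sample is enlarged.

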### Data management

To promote data quality, the data will be collected by well-trained assessor and the double entry of the data will be implemented by clinical research coordinators.

### Safety

Participants will also be monitored for any adverse events, including swelling, pain, bruise at the sites of needle insertion, or discomfort, palpitation, dizziness, etcetera after acupuncture treatment. Adverse effects will be recorded in the case report forms (CRF).

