## Background

Chemotherapy-induced nausea and vomiting (CINV) are common side-effects of many antineoplastic regimens and can occur for several days after treatment [1]. CINV significantly impacts the patient’ quality of life and nutritional status, and may lead to dose reduction or treatment discontinuation, subsequently increasing the risk of disease progression [2]. Although effective guidelines for CINV prevention exist for both moderately and highly emetogenic chemotherapies, adherence to these guidelines is not widely practiced because of their expensive costs and side-effects, such as headaches, dizziness, constipation, and insomnia [1].

Acupuncture treatment is one of the most sought-after therapeutic modalities in complementary and alternative medicine [3]. It is a safe medical procedure with minimal side effects. Evidence for the therapeutic effects of acupuncture on CINV exists [4]. Electroacupuncture for CINV management has been recommended by the American Society of Clinical Oncology [5]. Based on Traditional Chinese Medicine (TCM), the combination of acupoints can strengthen the essential and comprehensive therapeutic effects of acupuncture [6]. However, no consensus currently exists on the optimal acupoint combination for controlling CINV. For example, Gottschling S [7] found that stimulating PC6 (Neiguan), CV12 (Zhongwan), ST36 (Zusanli) and LI4 (Hegu) may effectively prevent CINV; Shen J [8] concluded that electro-acupuncture on PC6 (Neiguan) and ST36 (Zusanli) is more effective in controlling emesis than antiemetic pharmacotherapy alone. Therefore, we propose a randomized, controlled trial to determine the optimal combination of acupoints for CINV management.

In this trial, we aim to determine whether different acupoint combinations similarly manage CINV. We also aim to determine whether distal-proximal point association or local distribution point association more efficiently manages CINV.

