### Blinding

The evaluator and the statistician are blinded to the intervention a participant accepts. Acupuncturists and patients are not blinded to the treatments they deliver because of the nature of the intervention.

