#### Control groups

Participants in the control group received standard antiemetic alone. Standard antiemetic for all groups is based on the American Society of Clinical Oncology Clinical Practice Guideline [9]. 5-hydroxytryptamine-3 (5-HT3) antagonist (Ramosetron, Tropisetron) and dexamethasone will be administered before the chemotherapy treatment.

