	2e) Needle stimulation (e.g., manual, electrical)
	- Electrical stimulation: the frequency is 2/10 Hz, and the intensity of stimulation is adjusted according to the patient’s tolerance (maximum of 10 mA).
	2f) Needle retention time
	- Thirty minutes
	2g) Needle type (diameter, length, and manufacturer or material)
	- A disposable stainless steel acupuncture needle, 0.25mm × 40 mm (Huatuo, Suzhou Medical Co. Ltd., Jiangsu, China).
3.Treatment regimen	3a) Number of treatment sessions
	- Four treatment sessions in acupuncture groups.
	3b) Frequency and duration of treatment sessions
	- Once daily for 4 days, 30 minutes for each session.
4. Other components of treatment	4a) Details of other interventions administered to the acupuncture group (e.g., moxibustion, cupping, herbs, exercises, lifestyle advice)
	- No other interventions.
	4b) Setting and context of treatment, including instructions to practitioners, and information and explanations to patients
	- University hospitals. - Participants will be informed about acupuncture treatment in the study as follows: “In this study, eletroacupuncture for CINV will be used based on traditional Chinese medicine.”
5.Practitioner background	5) Description of participating acupuncturists (qualification or professional affiliation, years in acupuncture practice, other relevant experience)
	- The participating acupuncturists have all majored in acupuncture, have an acupuncture degree, and are qualified doctors of Tradition Chinese Medicine. All have at least 3 years of experience, and will have been trained in the standard operating procedure of electro-acupuncture on CINV. Thus, they are able to provide identical acupuncture treatment in accordance with a pre-defined protocol.
6. Control or comparator interventions	6a) Rationale for the control or comparator in the context of the research question, with sources that justify this choice
	- The control group is supplied with standard antiemetic alone, so as to provide patients with conventional treatment for CINV.
	6b) Precise description of the control or comparator. If sham acupuncture or any other type of acupuncture-like control is used, provide details as for items 1 to 3 above.
	- Participants in the control group will not receive acupuncture treatment.

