### Participant timeline

Enrollment will be conducted the day before chemotherapy (day 0). The electro -acupuncture intervention will be given once daily from day 1 to day 4. The schedule of enrollment, interventions, and assessments is shown in Table 2.

**Table 2 Tab2:** The schedule of enrollment, interventions, and assessments

	Study period								
	Enrolment	Allocation	Post-allocation						Close-out
Time points	-t1	t0	t1	t2	t3	t4	t5	t6-t20	t21
Enrollment									
Eligibility screen	√								
Informed consent	√								
Allocation		√							
Interventions									
Control group									
Experimental group I			√	√	√	√			
Experimental group II			√	√	√	√			
Experimental group III			√	√	√	√			
Assessments									
Baseline variables	√	√							
The frequency of nausea and vomiting		√	√	√	√	√	√	√	√
The grading of nausea and vomiting		√	√	√	√	√	√	√	√
Rhodes Index of nausea, vomiting and retching		√	√	√	√	√	√	√	√
The grading of constipation and diarrhea		√					√		√
eletrogastrogram		√					√		√
quality of life		√					√		√
anxiety and depression		√					√		√
Other adverse effect during the chemotherapy							√		√
The adverse effects of acupuncture			√	√	√	√			

t0, the day before chemotherapy; t1-t5, the first day to the fifth day of chemotherapy; t6-t21, the sixth day to the 21st day of chemotherapy

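### Non-needle symptoms such as dizziness are scheduled on days 1 to 4 only as acupuncture effects, so they have no concurrent background rate from the control group

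*Protocol article*

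**What the plan says.** The protocol article deals with adverse effects in several places.

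- **Safety.** "Participants will also be monitored for any adverse events". The examples are needle-site events (swelling, pain, bruise) and then more general symptoms: "discomfort, palpitation, dizziness, etcetera after acupuncture treatment".
- **Participant timeline, Table 2.** The row "The adverse effects of acupuncture" is ticked at t1, t2, t3 and t4. The row "Other adverse effect during the chemotherapy" is ticked at t5 and t21 and is not limited to a group.
- **Table 1, item 6b.** "Participants in the control group will not receive acupuncture treatment". There is no sham procedure.
- **Background.** Guideline antiemetics are said to have "side-effects, such as headaches, dizziness, constipation, and insomnia".
- **Control groups.** "Standard antiemetic for all groups is based on the American Society of Clinical Oncology Clinical Practice Guideline".
- **Blinding.** "Acupuncturists and patients are not blinded to the treatments they deliver because of the nature of the intervention".
- **Objectives.** The first objective includes the safety of the two kinds of point association.

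**The concern.** The control group is the only one without needling, so it alone can show how often dizziness and similar symptoms arise from chemotherapy and antiemetics. On t1 to t4, when these symptoms would be recorded as acupuncture effects, Table 2 schedules no adverse-effect check that can apply to control.

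Two things follow. First, a count of dizziness in the acupuncture row cannot be read as an effect of acupuncture, because the document itself names another cause that is present in every group. Second, if anyone later sets these counts beside control, the groups will have been observed on different schedules, and the likely direction is an apparent excess under acupuncture. Patients know their treatment, which may add to the labelling problem. Analysis cannot repair this afterwards, because control data not collected at t1 to t4 cannot be recovered.

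**Working it through.** No figure in the plan bears on this point, so there is none to reproduce. The check has two parts.

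**1. The schedule, side by side (Table 2, after allocation)**

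| Row | t1 to t4 | t5 | t21 | Can apply to control? |
|---|---|---|---|---|
| Acupuncture adverse effects | yes, 4 times | no | no | no |
| Other adverse effects during chemotherapy | no | yes | yes | yes |
| Frequency and grading of nausea and vomiting | yes, 4 times | yes | yes | yes |

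Scheduled adverse-effect assessments: 4 + 2 = 6 per acupuncture patient and 0 + 2 = 2 per control patient. The third row shows that every group is already assessed daily on t1 to t4 for nausea and vomiting.

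**2. Which symptoms have a documented competing cause**

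| Symptom in the Safety section | Listed as an antiemetic side effect in the Background? |
|---|---|
| Dizziness | yes |
| Palpitation | no |
| Discomfort | no |
| Swelling, pain, bruise at the needle site | not applicable; specific to needling |

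The overlap is documented for dizziness only. For palpitation and discomfort the point is just that their collection is unequal.

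**3. Illustration of size, on assumed inputs**

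The document gives neither a background rate of dizziness nor the share of events that control would miss. Assume no true acupuncture effect, the same true risk p in all groups, full capture in the acupuncture groups and capture c in control. Then:

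- apparent risk difference = p − p × c = p(1 − c)
- apparent risk ratio = p / (p × c) = 1/c

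| c | Risk ratio | Difference, p = 5% | p = 10% | p = 20% |
|---|---|---|---|---|
| 100% | 1.00 | 0 | 0 | 0 |
| 75% | 1.33 | 1.3 points | 2.5 points | 5.0 points |
| 50% | 2.00 | 2.5 points | 5.0 points | 10.0 points |
| 25% | 4.00 | 3.8 points | 7.5 points | 15.0 points |

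Example: p = 10%, c = 50% gives 10% − 5% = 5 points and 10/5 = 2.0.

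Suppose someone also pooled the acupuncture groups against control (180 against 60) and ran a two-sided pooled z-test at 5%. By exact binomial enumeration, c = 50% would give a significant result in about 7%, 19% and 42% of trials at p = 5%, 10% and 20%. At c = 100% the rate is about 5%, as it should be. The document specifies no such test.

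**The case against.** The strongest reply is that no distorted comparison is planned. The document specifies no test of acupuncture adverse effects against control. Its safety objective concerns the point associations, and the three acupuncture groups have identical safety schedules, so comparison among them is balanced. The row that can be compared with control is ticked at t5 and t21 in every group. Recording procedure-related events at the sessions where they can occur, with a separate all-group assessment, is a conventional layout. All of this stands. A reader might infer that the safety objective has no valid comparator, or that the trial's safety comparison is already biased; the document supports neither.

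Second, the Safety section speaks of participants and of any adverse events, without limiting this to the acupuncture groups, and describes no symptom checklist. Recording events in control on t1 to t4 is therefore not excluded, and the case report form, not shown, may settle how events are asked about and attributed. This stands in part: unscheduled recording is possible, but beside daily scheduled recording it still leaves ascertainment unequal.

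Third, the t5 row may be meant to cover the whole period since chemotherapy began. If that review recovers everything from t1 to t4, the bias is zero.

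A reader might also count six checks against two, treat each as an independent look with a fixed chance of finding the symptom, and arrive at large false-positive rates. At 5% per check this gives 1 − 0.95^6 = 26.5% against 1 − 0.95^2 = 9.8%, significant in about 83% of trials of 180 against 60; at 2% per check, 11.4% against 4.0% and about 40%. The arithmetic is right, but the document does not support the inputs. The per-check rates are invented, the two rows are never pooled in the plan, each check is taken to find only that day's symptom, and drop-out is ignored. With 20% drop-out (144 against 48) the same model gives about 74% and 30%.

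**Conclusion.** The concern holds in a limited form. As scheduled, non-needle symptoms on t1 to t4 are collected only as acupuncture effects, without a concurrent background rate from control, although the document names the antiemetic given to every group as a cause of one of them, dizziness. Any comparison of these symptoms with control would be open to unequal ascertainment, probably against acupuncture.

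Whether bias occurs, and how large it is, cannot be derived from the document. It ranges from none (complete capture at t5) to an apparent risk ratio of 2.0 if control captures half of the events and 4.0 if it captures a quarter; these capture shares are assumptions. Severity is minor: the issue concerns safety reporting only, and the primary outcomes and the sample size of 240 are unaffected.

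**What to change.** Split the acupuncture row of Table 2 in two.

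- **Non-needle symptoms (discomfort, palpitation, dizziness):** record in all four groups at t1 to t4, with the same questions on the same days, at the contacts that already collect nausea and vomiting. Report the proportion with each symptom by group with confidence intervals, without attributing it to acupuncture.
- **Needle-site events (swelling, pain, bruise):** keep in a row for the acupuncture groups only.

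With equal capture in all groups, the spurious risk difference is 0 and the risk ratio is 1.0.

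The cost is a few extra questions for control patients at contacts already scheduled, with no added visits, and a small change to the case report form. Because recruitment has begun, the change helps only patients enrolled after it. The report should state the date of the change and show patients enrolled before and after it separately for these symptoms. If the case report form already collects these symptoms in control on t1 to t4, a sentence in the Safety section and a corrected tick in Table 2 are enough.
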